#### Covariates

The analysis will include potential predictors of a provider’s baseline prescribing rate, as well as seasonality (table 2). These include a provider’s age, sex and employment status (full-time or part-time),^10^ and monthly practice patient composition (by age and sex).^19 32^ We will also use nested random intercepts for provider, practice group (clinic) and study site, representing within-group prescribing norms and a provider’s baseline willingness to prescribe after accounting for other predictors, as well as heterogeneity between study sites. Seasonality will be accounted for using a categorical variable for each month compared with January. An interaction term with study site will be included for each covariate to allow for differences in seasonal and demographic prescribing patterns between the two countries in our study.

**Table 2 T2:** Covariates included in the interrupted time-series analysis of the OPEN Stewardship Study

Variable	Purpose	Form	Description
Number of prescriptions	Outcome	Integer	Number of antimicrobial prescriptions for given indication
Number of visits for indication	Offset	Integer	Number of patient visits for given indication
Study site	Covariate	Binary	Southern Israel versus Ontario, Canada (baseline)
Practice group	Random intercept	ID	Random intercept for practice group (nested within region)
Provider	Random intercept	ID	Random intercept for provider (nested within practice group)
Month	Covariate	Categorical	Calendar month (baseline=January)
Month×study site	Interaction	Interaction	Allows different value for coefficients for Southern Israel
Physician age	Covariate	Integer	Physician age at *t_−12_*
Physician age×study site	Interaction	Interaction	Allows different value for coefficient for Southern Israel
Physician sex	Covariate	Binary	Female versus male (baseline)
Physician sex×study site	Interaction	Interaction	Allows different value for coefficient for Southern Israel
Physician employment status	Covariate	Binary	Part-time versus full-time (baseline)
Physician employment status×study site	Interaction	Interaction	Allows different value for coefficient for Southern Israel
Percent female patients	Covariate	Continuous	Percentage of visits by female patients
Percent female patients×study site	Interaction	Interaction	Allows different value for coefficient for Southern Israel
Percent patients 17 and under	Covariate	Continuous	Percentage of visits by patients 17 and younger
Percent patients 17 and under×study site	Interaction	Interaction	Allows different value for coefficient for Southern Israel
Percent patients 65 and older	Covariate	Continuous	Percentage of visits by patients 65 and older
Percent patients 65 and older×study site	Interaction	Interaction	Allows different value for coefficient for Southern Israel
Post-intervention	Intervention	Binary	1 if provider is in intervention group and intervention has occurred, 0 otherwise; level change of the outcome associated with intervention
Post-intervention×study site	Interaction	Interaction	Allows different value for level change of the outcome for Southern Israel
Time	Trend	Integer	Time since the beginning of the study; slope of the time trend of the outcome
Time×study site	Interaction	Interaction	Allows different value for slope of the time trend of the outcome for Southern Israel
Time×post-intervention	Intervention effect	Interaction	Change in slope of time trend in the intervention group after intervention is received
Time×post-intervention×study site	Interaction	Interaction	Allows different value for change in slope of time trend in the intervention group after intervention is received for Southern Israel

Excludes variables related to the effect of the COVID-19 pandemic.

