## Methods and analysis

### Objectives 1–4: non-randomised evaluation of intervention with interrupted time-series analysis.

#### Study design

Primary care physicians (providers) from two study sites will be voluntarily enrolled to participate in an antimicrobial stewardship intervention. The providers’ rates of antimicrobial prescribing after the intervention will be compared with their rates prior to having received the reports, as well as the prescribing rates of their peers in the same network who did not participate in the intervention. This study design is know as a controlled interrupted time-series.^26^ Our study design addresses the limitations of some previous studies of stewardship interventions, including small sample sizes, single-centre design, a lack of external controls and short follow-up.^16^

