#### Intervention

The intervention will consist of three personalised reports generated by the OPEN Stewardship platform and emailed to participants in the intervention group. The first report will be sent at the beginning of the intervention period (*t_0_*) and will consist of a welcome email followed by a benchmark of the provider’s overall antimicrobial prescribing rate relative to the average and 25th percentile of participants in the same network (UTOPIAN or CHS) during the previous year (2019). This report will also include guidelines highlighting that most conditions do not require more than 7 days of antimicrobials and a benchmark of the provider’s proportion of antimicrobial prescriptions with duration longer than 7 days relative to the average and 25th percentile of participants in the same network during the previous year. We chose to benchmark against other participants only (excluding non-participants) due to the expectation that those self-selecting into a stewardship intervention may already have lower rates of prescribing.

The two subsequent reports will be sent 3 (*t_3_*) and 6 (*t_6_*) months after the first report. These reports will target viral respiratory conditions (as defined by the primary International Classification of Diseases, Ninth Revision (ICD-9) code associated with the visit, see online supplemental table S1) and acute sinusitis, respectively, and will consist of a benchmark of the provider’s prescribing for the specified indication as well as site-specific best practice guidelines for the specified indication. The study concludes 1 year after the first report is sent (*t_12_*). The composition of each report is summarised in table 1. An example figure is shown in figure 1.

10.1136/bmjopen-2020-039810.supp1Supplementary data

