Stewardship interventions often result in a reversion to baseline behaviour after the intervention is discontinued.^35 36^ To examine the durability of the intervention effect, we will contrast the coefficients estimated from models including (1) all months in the post-intervention period, (2) the first 3 months in the post-intervention period, (3) the first 6 months in the post-intervention period. Finally, since the first report at *t_0_* (highlighting overall prescribing) is likely to affect objectives targeted by later reports (at *t_3_* or *t_6_*), for objectives 3 and 4, we will consider *t_0_* as an alternative start time of the post-intervention period.

As the COVID-19 pandemic represents a major disruption of primary care, its effect on prescribing will be modelled as one or more separate ‘intervention points’ in the time-series analysis.

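### The Table 2 model holds volunteers and controls within a site to one pre-intervention slope, so any existing difference in trend is estimated as an intervention effect

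*Protocol article*

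**What the plan says.** All references are to the protocol article.

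- **Study design** compares participants' rates after the reports with their own earlier rates, "as well as the prescribing rates of their peers in the same network who did not participate in the intervention", and calls this a controlled interrupted time-series.
- **Covariates, Table 2** gives the model. Time is "Time since the beginning of the study; slope of the time trend of the outcome". Its site interaction "Allows different value for slope of the time trend of the outcome for Southern Israel". Post-intervention is "1 if provider is in intervention group and intervention has occurred, 0 otherwise". Time×post-intervention is described as "Change in slope of time trend in the intervention group after intervention is received". Random intercepts are given for provider and practice group. The only stated omission from the table is the COVID-19 variables. No row separates intervention from control providers before the report, and none crosses group with time.
- **Intervention** expects that "those self-selecting into a stewardship intervention may already have lower rates of prescribing". **Participants** adds that volunteers may already be more engaged with stewardship.
- **Statistical analysis** models the effect as a level change, a slope change or both. It asks for a visual check that the pre-intervention trend is linear. It does not ask whether the trend is the same in both groups. For COVID-19, "its effect on prescribing will be modelled as one or more separate" intervention points.
- **Sensitivity analyses** adds a supplementary intention-to-treat analysis for Southern Israel, where the offer to enrol is randomised, and a comparison there of responders with non-responders.

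**The concern.** Post-intervention is 0 for every control month and for every volunteer month before the report. Before the report, then, nothing in the fixed part of the model tells the two groups apart. Within a site they have one slope, estimated mostly from controls (about 350 against 50 in Ontario; 250–300 against 50–100 in Southern Israel).

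Time×post-intervention is therefore the volunteers' post-report slope minus that shared slope. It is not the within-group change that its Table 2 description claims. If volunteers' prescribing was already falling faster than that of their peers, the model has nowhere to put the difference except the two intervention terms. A provider random intercept shifts a provider's level and cannot take up a slope.

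This affects all four prescribing objectives, in a design where volunteers select themselves.

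**Working it through.** **1. The plan's own figure.** Sample size gives rates of 0.126 and 0.107 per visit, 368 visits per month, one-sided α 0.05 and 90% power. Visits per group = (1.645 + 1.282)² × (0.126 + 0.107) / 0.019² ≈ 5527, and 5527 / 368 = 15.0 physicians. The stated figure of about 15 reproduces. It is a one-month comparison of two groups and says nothing about the level and slope terms.

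**2. Model for the check.** The log rate is regressed on Time, month-of-year, Post and Time×Post (Time centred at the report), with a provider random intercept, over 24 months. Expected coefficients are (X′V⁻¹X)⁻¹X′V⁻¹μ, with V = σ²(provider)·J + σ²(month)·I (J all ones, I the identity). The true effect is zero throughout.
- From the document: 24 months, split 12+12, 15+9 or 18+6 (Table 3); group sizes; 368 × 0.126 = 46.4 prescriptions per provider-month.
- Assumed: provider variance 0.16; monthly variance 1.5 / 46.4 = 0.032 (or 0.05) for a frequent outcome and 0.5 to 1.0 for a sparse one; the size of any drift.
- Left out: practice intercept, demographic covariates, COVID-19 terms.

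**3. Difference in trend.** With 12+12 months, the mean post month is 12 months after the mean pre month, so the bias of a level-only model is close to 12 × the monthly drift.

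| Assumed drift of volunteers relative to controls | Table 2 model | Group and group×time added |
|---|---|---|
| −0.005/month, 50 v 350, level only | −0.060 (SE 0.011), over 5 SE | 0 (SE 0.022) |
| Same, level and slope | −0.035 and −0.0047/month | 0 and 0 |
| −5%/year, 150 v 600, mean post-period effect, objective 1 | −5.1% | 0 |
| −10%/year, same | −10.1% | 0 |

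In the second row, −0.0047 of the −0.005 drift (94%) appears as a change in slope, although the volunteers' own slope never changed. For objectives 3 and 4 the spurious effect is −4.8% and −4.7% at 5% per year, and −9.7% and −9.4% at 10%. A group indicator without group×time leaves −5.0% at 5% per year.

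Simulated negative binomial counts (300 data sets per cell), analysed on the log rate with a random intercept, agree. At 5% per year, a nominal 5% test rejects in 98% of data sets (150 v 600) and 69% (50 v 350). With group and group×time added, rejection is about 3–7%.

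**4. Difference in level.** For objective 1 at 50 v 350, a constant gap of −0.15 leaks only −0.0025 into the effect, under 2% of the gap. With variances 0.5 (monthly) and 0.16 (provider) the leak is −0.031. With 1.0 and 0.10 it is −0.068, or 45% of the gap, against a level-only SE of 0.054. A group indicator removes it in each case.

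**5. A common shock.** Suppose a 3-month dip of −0.2 in both groups just before the report is missed by the COVID-19 terms. The level-only effect is 0. With level and slope it gives −0.055 and +0.010/month, and −0.055 + 5.5 × 0.010 = 0 over the 12 post months. Adding group and group×time alone raises the slope artefact to +0.019/month. Calendar-month effects remove it.

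**The case against.** Parallel trends with provider intercepts is a recognised difference-in-differences-type specification. What the protocol says about volunteers concerns their level and engagement, not a diverging slope. This stands: the size of the drift is assumed, and nothing in the document shows that one exists. It does not rescue the plan. Parallel trends is neither stated nor checked, and Table 2 describes its slope term as something it does not estimate.

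Two stronger readings are tempting and not supported. A reader might infer that a baseline difference in level is also reported as an effect. For objectives 1 and 2 the provider intercept absorbs nearly all of it; leakage matters only if the indication-specific counts of objectives 3 and 4 are sparse, and the document does not give those counts. A reader might also infer that a COVID-19 shock biases the result. That presumes the planned COVID-19 terms fail, and even then the average post-period effect under Table 2 is zero; only the separate level and slope coefficients are distorted.

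The intention-to-treat analysis is a real safeguard against self-selection where the offer is randomised. It is supplementary, covers Southern Israel only, and leaves Ontario unprotected.

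The article may condense a fuller analysis plan. But this is not a missing detail: Table 2 sets out the model, and its only stated omission is the COVID-19 variables.

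**Conclusion.** The point holds for trend. As written, the model cannot separate a prior within-site divergence between volunteers and controls from an intervention effect. The spurious effect is roughly one year's worth of the differential: about 5% for 5% per year and about 10% for 10% per year, the latter two thirds of the 15% target (10/15). These sizes rest on the assumed drift; the estimate of bias changes little across the group sizes tried. False-positive rates and standard errors depend also on the assumed variances. For level the point holds only in a limited form, for sparse outcomes. The shared slope is within site, since Time×study site is in the model.

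**What to change.** - Add an intervention-group indicator and group×time to Table 2, each with its site interaction.
- Define the effect as the departure from the group's own pre-intervention trend, relative to controls.
- Report the comparison of pre-intervention trends between groups, and keep the present shared-slope model as a sensitivity analysis.
- Optionally, replace Time, month-of-year and the COVID-19 points by site-specific calendar-month effects, since group×time alone does not clear a common shock from the level and slope coefficients.

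No new data are needed for the added terms; the cost is precision. A 15% reduction is ln(0.85) = −0.163.
- **Objective 1, 50 v 350, level only:** the SE goes from 0.011 to 0.022, leaving 0.163 / 0.022 ≈ 7 SE. For the mean post-period effect with a slope term (150 v 600, monthly variance 0.05), it goes from 0.0083 to 0.0211, about 2.5 times.
- **Objectives 3 and 4, if sparse (assumed variances 1.0 and 0.10, 50 v 350, level only):** the SE goes from 0.058 to 0.112 and from 0.067 to 0.102. A 15% reduction falls from about 2.8 to 1.5 SE and from about 2.4 to 1.6 SE.

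The plan should state this loss for objectives 3 and 4.

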#### Statistical analysis

We will perform a multilevel, controlled interrupted time-series analysis with the provider as the unit of analysis.^33^ A negative binomial model (to allow for overdispersion of the outcome) will be used with prescribing rates as the outcome. Each provider in the intervention group will contribute 24 observations: a minimum of 12 months in the pre-intervention period (*t_−12_* to *t_0_*) and up to 12 months in the post-intervention period, depending on the objective. The pre-intervention and post-intervention periods of each outcome are defined by the time when the relevant report was delivered. The first report (*t_0_*) corresponds to objectives 1 and 2, the second report (*t_3_*) to objective 3 and the third report (*t_6_*) to objective 4. The pre-intervention and post-intervention periods of each objective are summarised in table 3. Providers in the external control group will contribute 24 observations in the control period. The timeline of the study for each objective is shown in figure 2.

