**Figure 1 F1:**
[figure not shown]
Example of chart sent in the first feedback report, representing the provider’s prescribing rate/100 visits for any indication versus the average rate and 25th percentile rate across all providers in the study from the same study site.

**Table 1 T1:** Composition of the feedback reports (intervention) at each time point

Feedback report	Content of report	Benchmarking figure	Guidelines
Report at *t_0_*	1. Antimicrobial prescribing rate/100 visits in the previous year for all visits. 2. Proportion of antimicrobial prescriptions in the previous year with duration over 7 days.	Provider’s own rate/proportion versus average rate/proportion and 25th percentile rate/proportion across all participants at the same study site.	Guidelines indicating that antimicrobial prescribing longer than 7 days is not necessary for many conditions.
Report at *t_3_*	1. Antimicrobial prescribing rate/100 visits in the previous year for viral respiratory conditions.	Provider’s own rate versus average rate and 25th percentile rate across all participants at the same study site.	Prescribing guidelines for viral respiratory conditions.
Report at *t_6_*	1. Antimicrobial prescribing rate/100 visits in the previous year for acute sinusitis.	Provider’s own rate versus average rate and 25th percentile rate across all participants at the same study site.	Prescribing guidelines for acute sinusitis.

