**Figure 2 F2:**
[figure not shown]
Pre-intervention and post-intervention periods for objectives 1–4 of the OPEN Stewardship Study. (A) Objective 1, overall prescribing (report sent at *t_0_*). (B) Objective 2, prescribing with duration longer than 7 days (report sent at *t_0_*). (C) Objective 3, prescribing for viral respiratory conditions (report sent at *t_3_*). (D) Objective 4, prescribing for acute sinusitis (report sent at *t_6_*). *t_0_* represents the time of the first report (intervention); *t_−12_* represents 1 year prior to the first report; *t_12_* marks the conclusion of the study period (1 year after the first report).

**Table 3 T3:** Timing of analyses for objectives 1–4 of the study

Objective	Outcome	Unit of analysis	Intervention time	Number of observations in intervention cohort		Total observations/observations in control cohort
				Pre-intervention	Post-intervention	
1	Prescribing for all indications	Provider	*t_0_*	12	12	24
2	Prescribing (for all indications) with duration longer than 7 days	Provider	*t_0_*	12	12	24
3	Prescribing for viral respiratory conditions	Provider	*t_3_*	15	9	24
4	Prescribing for acute sinusitis	Provider	*t_6_*	18	6	24

The definitions of the pre-intervention and post-intervention periods are dependent on the delivery time of the report (intervention) related to each objective.

The intervention effect will be modelled as a level change and/or change in slope for the prescribing rate at the beginning of the post-intervention period.^26^ An interaction term with study site will be included to allow for differences in the intervention effect between Ontario and Southern Israel. A key assumption of interrupted time-series analysis is that the pre-intervention time trend is assumed to be linear, which must be evaluated through visualisation.^34^ Otherwise, non-linear terms may be considered. Model fit can be assessed by comparing models containing intervention parameters to a null model not containing intervention parameters using a statistic such as Akaike information criterion.

Autocorrelation in each provider’s time-series should be accounted for by the random intercept (provider nested within practice group nested within study site) and by controlling for seasonality (categorical variable for month).^26^ In case autocorrelation is present in the residual distribution, an autoregressive covariance structure will be considered.

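### Objectives 3 and 4 count 3 of 15 and 6 of 18 months after the first report as pre-intervention, so their main estimate is neither the targeted report's effect nor the total effect

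*Protocol article*

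**What the plan says.** In the protocol article, Statistical analysis sets the boundary separately for each outcome: "The pre-intervention and post-intervention periods of each outcome are defined by the time when the relevant report was delivered". It assigns the reports as follows: "The first report (*t_0_*) corresponds to objectives 1 and 2, the second report (*t_3_*) to objective 3 and the third report (*t_6_*) to objective 4". Table 3 reads "Prescribing for viral respiratory conditions Provider *t_3_* 15 9 24" for Objective 3 and "Prescribing for acute sinusitis Provider *t_6_* 18 6 24" for Objective 4, and the footnote repeats the rule.

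Table 2 has one binary post-intervention term for participants and one change in slope, each with a study-site interaction. It has no separate term for an earlier report. Time is common to participants and controls before the intervention.

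Table 1 shows that the first report benchmarks this: "Antimicrobial prescribing rate/100 visits in the previous year for all visits". That includes visits for viral respiratory conditions and acute sinusitis. Later in Statistical analysis the authors write that this report "is likely to affect objectives targeted by later reports" and say they will consider t0 as an alternative start for Objectives 3 and 4.

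The Intervention section defines the intervention as the three reports together. Study approach and objectives states each objective as the impact of the stewardship intervention, after it against before it and against physicians who did not receive it.

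**The concern.** For Objectives 3 and 4 the main analysis uses a baseline that the authors themselves expect to be affected by the intervention. If report 1 lowers prescribing for these indications, the baseline is already lowered and part of the intervention's effect is subtracted from itself. The rest of report 1's effect is still in the post period, where it is credited to the later report. The result is too small as a total effect and wrongly attributed as an effect of the targeted report. For Objective 4 three reports can be mixed, because report 2 at t3 also falls inside the 18 months labelled pre-intervention.

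At stake is the interpretation of two of the four prescribing objectives: a reader could conclude that a message on sinusitis or viral respiratory conditions worked when the general benchmark did the work.

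**Working it through.** **1. Table 3 reproduced.** Baseline runs from t-12 to t0, 12 months; follow-up from t0 to t12, 12 months.
- Objective 3, boundary t3: 12 + 3 = 15 pre, 12 − 3 = 9 post. Exposed pre months: 3/15 = 20%.
- Objective 4, boundary t6: 12 + 6 = 18 pre, 12 − 6 = 6 post. Exposed pre months: 6/18 = 33%. Of these six, 6 − 3 = 3 also follow report 2.

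**2. What a single step estimates.** Let b1, b2 and b3 be permanent log rate ratios for reports 1, 2 and 3 in participants. The step is approximately the post mean minus the pre mean, relative to controls:
- Objective 3: b2 + (1 − 3/15)·b1 = b2 + 0.80·b1. The total effect is b1 + b2.
- Objective 4: b3 + (1 − 6/18)·b1 + (1 − 3/18)·b2 = b3 + 0.67·b1 + 0.83·b2. The total effect is b1 + b2 + b3.

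**3. Illustrative sizes.** These are assumptions. The 15% is the clinically meaningful reduction in the Sample size section, which refers to overall prescribing. I fitted a noise-free Poisson log-linear model with the Table 2 structure: a group effect in place of the random intercepts, a common trend, month terms and one participant step, with 50 participants, 350 controls and a single t0.

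| Scenario | Objective | Approximation | Model fit | Targeted report, true | Total, true |
|---|---|---|---|---|---|
| Report 1 only, 15% cut | 3 | 0.85^0.80 = 0.878 | 0.879 | 1.00 | 0.85 |
| Report 1 only, 15% cut | 4 | 0.85^0.67 = 0.897 | 0.899 | 1.00 | 0.85 |
| Report 1 and targeted report, 10% each | 3 | 0.90^1.80 = 0.827 | 0.828 | 0.90 | 0.81 |
| Report 1 and targeted report, 10% each | 4 | 0.90^1.67 = 0.839 | 0.841 | 0.90 | 0.81 |
| All three reports, 10% each | 4 | 0.90^2.50 = 0.768 | 0.769 | 0.90 | 0.729 |

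Adding the slope change at the same boundary leaves these level estimates unchanged.

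**4. The t0 alternative, level only.**
- Report 1 only, 15% cut: 0.85 for both objectives, the true total.
- Two 10% cuts: (3 × 0.90 + 9 × 0.81)/12 = 0.833 for Objective 3 and (6 × 0.90 + 6 × 0.81)/12 = 0.855 for Objective 4. These are 12-month averages as the reports accumulate, against 0.81 at the end of the study.

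**5. One step per report.** Steps at t0 and t3 (Objective 3), or at t0, t3 and t6 (Objective 4), recover 0.90 for every report in the 10% scenarios. Two steps are not enough for Objective 4: with all three reports at 10%, steps at t0 and t6 alone give about 0.85 for report 3 instead of 0.90.

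**6. Precision of the incremental effect**, with independent monthly errors of equal variance. Standard error with separate steps relative to the planned single step:
- Objective 3: √[(1/3 + 1/9)/(1/15 + 1/9)] = 1.58; with the common trend and month terms, 1.55.
- Objective 4, three steps: √[(1/3 + 1/6)/(1/18 + 1/6)] = 1.50; with the common trend and month terms, 1.48.

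**The case against.** The protocol discloses the spill-over and offers a t0 start. Its objectives concern the whole intervention, and none asks for the separate effect of each report. A t0 start has a clean 12-month baseline, fits the objectives as written and returns the true 0.85 when only report 1 acts. A gap between the t0 and the t3/t6 results would also warn the analyst. All sizes depend on report 1 affecting these outcomes. If no earlier report does, the t3/t6 estimate is not biased in this way.

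Much of this stands. A reader might infer that the plan overlooks the problem or cannot estimate the total effect; the documents support neither. A reader might also infer that a real effect could vanish into the participants' baseline trend. That would need a participant-specific pre-intervention trend, which Table 2 does not contain, so it cannot be held against this plan.

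What remains is that t0 is only to be considered. The text and Table 3 keep t3 and t6 as the main boundaries, although by the objectives' own definition the intervention began at t0. If the later boundaries are meant to capture the targeted report, a single step does not do that, and neither does the t0 alternative.

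**Conclusion.** The point holds for the main analyses of Objectives 3 and 4. That 20% and 33% of the pre-intervention months follow report 1 is a matter of counting and needs no assumption. The mixing requires only a non-zero effect of an earlier report, which the protocol calls likely for report 1.

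The size is not known. Under permanent step effects, the planned coefficient carries about 80% (Objective 3) or 67% (Objective 4) of report 1's log effect on top of the targeted report's own, and for Objective 4 about 83% of any report 2 effect. When the effects share a direction the total is understated only modestly, for example 0.83 or 0.84 against 0.81. Attribution to the targeted report suffers more: 0.88 or 0.90 against a true 1.00 when only report 1 acts. Objectives 1 and 2, whose boundary is t0, are not affected.

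**What to change.** For Objectives 3 and 4:
- Use t-12 to t0 as the baseline in the main analysis.
- Name the t0-start effect as the main estimate of the total intervention effect, and say that its level term averages over the 12 months.
- Add one participant step per report, at t0 and t3 for Objective 3 and at t0, t3 and t6 for Objective 4. Report the last step as the targeted report's incremental effect. The product of the steps gives the end-of-study total.
- Correct Table 3 to 12 pre-intervention months followed by the report phases: 3 + 9 months for Objective 3 and 3 + 3 + 6 for Objective 4. Align the period rule in the text and Figure 2.

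Cost: one extra model term for Objective 3 and two for Objective 4 (plus site interactions if kept), and no new data. The loss of precision is not slight. Under the error assumption above, the incremental effect's standard error is about 55% larger for Objective 3 and about 50% larger for Objective 4 than that of the planned single step. This is a reason to make the total effect the main result and the incremental effect a supporting one.
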